#### Secondary Outcome Analysis

Consistent with the secondary analyses of the primary outcome described in the preceding section, all secondary outcomes will be analyzed using patient-level segmented regression analyses with terms for time, intervention, time after intervention, and the following covariates: age, sex, type of MI, prior MI, prior cardiac medication use, and site. The remaining secondary outcomes (time to hospitalization for cardiovascular disease, hospitalization due to repeat acute MI, hospitalization due to stroke, repeat cardiac catheterization, coronary revascularization, and death) will be analyzed at the patient level using Cox proportional hazards regression. Death will be treated as a censoring event for analyses of nonfatal, time-to-event outcomes.

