### Data Sources

The following administrative databases held at ICES McMaster will be linked and analyzed for the MIPAD study: (1) CorHealth Cardiac Registry (CCN-CR), which is a clinical database containing information such as demographics, comorbidities (eg, diabetes, hypertension, prior heart disease), and procedure-specific details (eg, referral date, patient wait time, complications, results) for patients who undergo a cardiac procedure (eg, cardiac catheterization, percutaneous coronary intervention, or coronary artery bypass graft surgery) in Ontario [26]; (2) Canadian Institute for Health Information Discharge Abstract Database, which captures demographic, clinical, and administrative information on all hospital inpatient discharges (including deaths, sign-outs, and transfers) in all provinces and territories except Quebec; (3) National Ambulatory Care Reporting System, containing data for all ambulatory care provided in hospital (eg, day surgeries and emergency department visits) or in the community across Canada; (4) ODB database, which captures all prescription medication dispensations for Ontario residents covered under the ODB plan (including those aged 65 years and older); (5) Ontario Health Insurance Plan database, covering physician billings for procedures and consultations; and (6) Registered Persons Database, containing demographic information (including date of death) on all persons registered under the Ontario Health Insurance Plan, which is the majority of Ontario residents. The CCN-CR has been used for numerous quality assurance and research projects, including 1 observational and 1 randomized controlled trial (RCT) conducted by the principal investigators of the MIPAD study [4,27]. Several provinces and territories (including Ontario) also use the Canadian Institute for Health Information Discharge Abstract Database to capture day surgeries [28]. Of the 5 recommended cardiac medication classes post-MI, aspirin (primary antiplatelet) is poorly captured in the ODB, as most dispensations are private pay. Correspondingly, measurement of medication adherence in this study will only concern statins, beta blockers, angiotensin system inhibitors, and secondary antiplatelets.

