The aforementioned segmented regression analyses will compare pre-intervention to post-intervention levels and trends within intervention groups; therefore, groups will act as their own internal controls. Additionally, we will compare these changes to changes observed in the control group (ie, all other hospitals in Ontario). Analysis of the parallel control group — which will be identically specified to the intervention group analyses — will help address threats to internal validity, such as co-occurring interventions or other policy changes that could be rival explanations for any observed changes in our intervention series. In other words, if we detect a post-intervention effect in the parallel control group, it suggests that changes in the underlying patient population or another (unidentified) intervention could have occurred around the same time across Ontario hospitals that might explain away any observed intervention effects.

To account for potential differences in patient case mix over time and among sites, we will conduct additional secondary analyses of the primary outcome with the patient as the unit of analysis. We will use segmented binary logistic regression analysis with terms as specified in previous paragraphs and with the addition of the following patient covariates: age, sex, type of MI (STEMI vs non-STEMI), prior MI, prior cardiac medication use, and site.

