## Discussion

Based on previous observational studies [4,15,16], it is expected that long-term cardiac medication adherence among post-MI patients will improve following the implementation of a standardized discharge prescription length of 90 days with 3 repeats, in conjunction with educational outreach and support, as compared to usual care. Specifically, it is expected that the PDC will improve in each cardiac medication class. The PDC is considered a validated measure of medication adherence [38], and patients with a PDC ≥80% have been shown to have better clinical outcomes [34]. We do not expect that this intervention will increase the number of cardiac medications prescribed to post-MI patients at discharge; rather, we anticipate that standardized discharge prescription forms (in combination with education) will improve long-term adherence to the cardiac medications initiated at discharge.

Previous studies have demonstrated that a 10% increase in cardiac medication adherence in the setting of secondary prevention can result in a 6.7% relative reduction in major adverse cardiac events (MACE), including but not limited to death, MI, stroke, and revascularization procedures [38,39]. Assuming the 1-year MACE rate is 14.7% (based on a very large and high-quality RCT) [40] and estimating that there are approximately 3000 MIs in the study region in 1 year, we would expect the implementation of our intervention to prevent over 30 MACE per year and significantly reduce direct health care expenditures. This estimate only accounts for direct hospitalization costs and does not reflect other costs including rehabilitation, home care, and indirect community care costs. The cost implications of longer cardiac prescriptions at discharge are expected to be very minimal, with a surplus of medications likely administered in a minority of cases.

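### The patient-level models, meant to adjust for case mix, use a closed covariate list that omits diabetes, hypertension and prior heart disease other than MI, although the linked registry records them

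*Protocol article*

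**What the plan says.** The Primary Outcome Analysis section of the protocol gives the reason for the patient-level models: "To account for potential differences in patient case mix over time and among sites". It then lists six covariates. The Secondary Outcome Analysis section applies the same set to the secondary outcomes, in segmented models fitted to individual patients. Its wording for the adjustment set is "and the following covariates: age, sex, type of MI, prior MI, prior cardiac medication use, and site". Nothing marks the list as illustrative.

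The next sentence in that section says that the clinical events and death "will be analyzed at the patient level using Cox proportional hazards regression". It names no covariates and no time terms.

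The Data Sources section says the cardiac registry contains "demographics, comorbidities (eg, diabetes, hypertension, prior heart disease), and procedure-specific details", and that it covers patients having "cardiac catheterization, percutaneous coronary intervention, or coronary artery bypass graft surgery". Under Recruitment, every patient enters the cohort through a registry claim for catheterization, so every patient has a registry record.

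**The concern.** Sites were not randomized. They were a convenience sample in one region, and the effect is read from a before-and-after contrast within them. Adjustment is the protocol's own answer to changes in who is treated. Diabetes, hypertension and earlier heart disease plausibly predict death, cardiovascular readmission and repeat revascularization. They sit in a source that is already linked, and no reason is given for leaving them out.

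The clinical effect in view is small. The Discussion cites a 6.7% relative reduction in major adverse cardiac events for a 10% gain in adherence, a ratio of about 0.933. An effect of that size can be imitated or hidden by a fairly moderate change in the patients' baseline risk.

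**Working it through.** **Inputs from the protocol.** 3000 MIs per year, a 1-year event rate of 14.7% and a 6.7% relative reduction (Discussion); 60 patients per month per site, 24 months before and 12 after (Power Calculation); the covariates and time terms (Secondary Outcome Analysis).

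**Inputs assumed.** The documents give no prevalence, no change in prevalence and no hazard ratio for the omitted comorbidities. I take hazard ratios (HR) of 1.5 and 2, a prevalence of 35% (20% to 70% in step 3), and independence from the six listed covariates.

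**1. The protocol's yardstick.** 3000 × 0.147 = 441 events; 441 × 0.067 = 29.5 prevented. The Discussion says over 30, so the figure is reproduced apart from rounding.

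**2. Shift from one omitted comorbidity.** When prevalence moves from p0 to p1, the average hazard changes by the factor (1 + p1(HR − 1)) / (1 + p0(HR − 1)).

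| Step from 35% | HR 1.5 | HR 2 |
|---|---|---|
| 5 points, to 40% | 1.200/1.175 = 1.021 | 1.40/1.35 = 1.037 |
| 10 points, to 45% | 1.225/1.175 = 1.043 | 1.45/1.35 = 1.074 |

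The range is 2.1% to 7.4%. Only the last cell reaches 6.7%.

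**3. Step needed to match 6.7%.** Solving the same formula for a ratio of 0.933 or its inverse, with starting prevalence between 20% and 70%, gives about 8 to 12 points at HR 2 and 15 to 19 points at HR 1.5. For example, at HR 2 a fall from 35% to 26% gives 1.26/1.35 = 0.933.

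**4. Several factors at once.** With four omitted factors (assumed prevalences 35%, 70%, 30% and 30%) all moving the same way, 4 points each gives 6.8% at HR 1.5. At HR 2, 2 points each gives 5.9% and 3 points each gives 8.9%.

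**5. What the time terms absorb.** I fitted a purely linear drift of 0.005 per month by least squares on the segmented design (intercept, time, intervention, time after intervention; 36 months). The coefficients are 0, 0.005, 0 and 0. The whole drift goes into the time term, and the level and slope changes are unbiased.

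**6. Sampling error for comparison.** Two sites give 2 × 60 × 36 = 4320 patients and, using 14.7% as a stand-in rate, about 635 events. In a simple before-and-after comparison the standard error of the log hazard ratio is 1/√(635 × 2/9) = 0.084, and power for 0.933 is about 13%. For the segmented level term, power is about 6% and the 95% confidence limits lie a factor of about 1.4 either side of the estimate.

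**The case against.** A reader might infer that case-mix drift as large as the expected benefit does remain in the hazard ratios. The documents do not support that. They give no drift, and three of the four assumed scenarios in step 2 fall short of 6.7%. Where the segmented terms apply, gradual linear drift does no harm, and the site term removes stable differences between sites. The parallel control group is a further check on province-wide change. It is described for the primary outcome, however, and cannot reveal a shift confined to the intervention sites.

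Existing coverage also counts. Prior MI captures part of prior heart disease, and prior cardiac medication use may partly stand in for hypertension and cardiac history. To that extent the independence assumed in step 2 overstates the shift.

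Index revascularization is a weaker case than the comorbidities. The protocol names the procedures the registry covers, not an index-treatment field. Coronary revascularization within 365 days is itself an outcome, so a covariate without a time limit could overlap with it.

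Two further points stand. In logistic and Cox models, adding prognostic covariates does not generally narrow the interval for the treatment effect, so a gain in precision is not part of this point. And a shift of 2% to 4% is well inside the sampling error in step 6, for outcomes that are secondary.

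None of this explains why recorded comorbidities are left out of models whose stated purpose is case-mix control. The protection from the time terms is also uncertain where it matters most, because the Cox sentence does not clearly inherit them or the covariates. If those models have no segmented terms, gradual drift would enter the hazard ratios as well.

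**Conclusion.** The point holds in a limited form. The covariate list is a stated choice, it serves case-mix control, and it omits diabetes, hypertension and prior heart disease other than MI although the registry holds them. The size of any resulting bias is unknown. With hazard ratios of 1.5 to 2, a starting prevalence of 35% and no correlation with the listed covariates, a 5- to 10-point step in one comorbidity at September 2017 would move the hazard by about 2% to 7%, against an expected 6.7%. Under the segmented terms, only such a step or a change of slope matters. Whether those terms and the covariates reach the Cox models is unclear from the text. This is an inexpensive improvement to the secondary analyses and to the adjusted analysis of the primary outcome; it does not touch the aggregate primary analysis.

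**What to change.** In both the Primary and the Secondary Outcome Analysis sections, add diabetes, hypertension and prior heart disease to the patient-level covariates, for all three groups, or give the reason for leaving them out. Add revascularization only if the registry records it, and only when performed during the index admission before discharge, so that it cannot overlap with the 365-day outcome. State that the Cox models carry the same covariates together with the time, intervention and time-after-intervention terms.

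The cost is a slightly longer covariate list. No new data are needed, and with thousands of patients (4320 for two sites on the protocol's own accrual figure) the loss of degrees of freedom is negligible.

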#### Power Calculation

Using the simulation approach developed by Zhang et al [37], we determined that 24 pre-intervention and 12 post-intervention data points (collected at monthly intervals) in each of the 2 intervention groups will achieve 80% power to detect an immediate absolute increase (ie, intercept change) of 10% in the monthly proportion of patients deemed adherent to their recommended cardiac medications using a likelihood ratio test at the 5% level of significance. The anticipated baseline proportion of patients with cardiac medication adherence (ie, average PDC ≥80%) is 75%. The simulation assumed a mean square error for the monthly proportions of 3.1% with 60 patients per month per site, a pre-intervention trend of 0, and an autocorrelation parameter of 0.3.

#### Health Economic Evaluation

We hypothesize that this intervention package is at least cost neutral and potentially demonstrates cost savings when compared to current practice. The cost implications of longer cardiac prescriptions at discharge are expected to be very minimal, with a surplus of medications likely administered in only a minority of cases. We will collect data that will allow us to determine (1) the added costs of medication surplus (ie, wastage) with longer prescriptions in the intervention versus usual care or control periods, (2) the difference in health system costs associated with cardiovascular disease events in the intervention versus usual care or control periods, and (3) the potential for cost savings due to projected reduction in cardiovascular disease events and reduced prescription fees with longer discharge prescriptions.

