#### Standardized Discharge Prescription Forms

We implemented a revised standardized discharge prescription form available on all wards where MI patients are managed. The revised prescription form has a default of a 90-day supply with 3 repeats for recommended cardiac medications (ie, primary antiplatelet [aspirin], statin, beta blocker, angiotensin system inhibitor, and secondary antiplatelet). Current discharge prescription forms leave the dispensation amount and repeats to the discretion of the individual physician. To encourage community pharmacists to dispense 90 days’ worth of medications at discharge, in accordance with the revised discharge prescriptions, the Ontario Pharmacists Association recommended that the following statement be included on the discharge prescription: “Override trial dispensation as these medications were initiated in hospital, Use code NH.” This is a standard mechanism to ensure patients with drug coverage from a provincial payer (ie, the Ontario Drug Benefit [ODB] Plan) receive the correct amount of medications on their first fill post-discharge. See Figure 3 for a copy of the discharge prescription form and highlighted revisions. The intervention may be tailored by the physician to allow shorter discharge prescription durations for cost consideration in patients less than 65 years of age and without medication insurance. Monthly monitoring with intervention group 1 ward visits ensured standardized prescription forms were being implemented.

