#### Education

The education-based intervention consists of both components detailed in the following sections.

For educational outreach to the hospital staff, educational rounds for all involved health care providers (eg, physicians, residents, nurses) at each of the 6 sites took place at the start of the intervention period to outline the evidence regarding longer prescriptions at discharge and encourage this change in discharge practices. In a preliminary survey of 82 health care providers in the study region, 95% said they would use standardized discharge prescriptions with 3 months of cardiac medication supplies and 3 repeats but less than 50% admitted that they currently provide medication supplies to cover a year ([name], unpublished data). Further education (eg, emails, mailouts, site visits) occurred every 3 months during the intervention period.

For educational support of community pharmacies, in addition to the statement “Override trial dispensation as these medications were initiated in hospital, Use code NH” added to the discharge prescriptions, outreach via personal emails and newsletters to community pharmacies in the study region was undertaken with help from the Ontario Pharmacists Association and Ontario Pharmacy Evidence Network. This outreach was intended to help ensure fidelity of the intervention when medications were dispensed at discharge.

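### The economic evaluation counts only wasted drug as added drug cost, omitting the extra drug used when adherence rises and the cost of delivering the package

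*Protocol article*

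**What the plan says.** The Health Economic Evaluation section of the protocol article opens with a hypothesis about the whole package: "We hypothesize that this intervention package is at least cost neutral and potentially demonstrates cost savings when compared to current practice". It then lists three quantities for the collected data to establish:

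- Item 1, on drug cost: "the added costs of medication surplus (ie, wastage) with longer prescriptions in the intervention versus usual care or control periods".
- Item 2, on observed events: how far spending by the health system on cardiovascular events differs between intervention periods and comparison periods.
- Item 3, on savings: "the potential for cost savings due to projected reduction in cardiovascular disease events and reduced prescription fees with longer discharge prescriptions".

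That section and the Discussion both expect minimal cost implications, and the only reason either gives is that surplus drug should arise in a minority of cases.

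On mechanism, the Discussion says "it is expected that the PDC will improve in each cardiac medication class". The Primary Outcome section derives the proportion of days covered (PDC) from ODB claims.

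On delivery, the Education section describes start-up rounds at the 6 sites and outreach to community pharmacies, and adds: "Further education (eg, emails, mailouts, site visits) occurred every 3 months during the intervention period". The Standardized Discharge Prescription Forms section adds: "Monthly monitoring with intervention group 1 ward visits ensured standardized prescription forms were being implemented".

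**The concern.** The hypothesis concerns the net cost of the package, but the cost side of the list has one entry: drug that is dispensed and not used. Two costs are absent. The first is the drug that patients go on to use because adherence improves, which is the intended effect and the source of any averted events. The second is the work of delivering the package. The list therefore takes in the benefit of extra treatment without its drug cost, and the omitted drug term grows as the intervention becomes more effective.

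Cost is the second objective in the Abstract. The Strengths section names cost limitations as the only foreseeable risk and says the economic analysis will evaluate them. A favourable cost finding could then reflect which items were listed rather than the data.

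**Working it through.** **Step 1: the article's own figure.** The article states no cost figure. The nearest is the Discussion's projection: "we would expect the implementation of our intervention to prevent over 30 MACE per year and significantly reduce direct health care expenditures". Its inputs are about 3000 MIs a year, a 1-year MACE rate of 14.7% and a 6.7% relative reduction. 3000 × 0.147 × 0.067 = 29.5. This reproduces the stated figure within the rounding of an approximate 3000 (3,046 MIs would give 30). It is an event count and puts no value on any item in the list.

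**Step 2: what a net cost contains.** For intervention against usual care, per patient:

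net cost = Δ(drug used) + Δ(drug wasted) + Δ(dispensing fees) + Δ(event costs) + delivery

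Here drug dispensed = drug used + drug wasted. Covered days stand in for use, since claims cannot show whether pills were taken (Limitations).

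| Term | Where listed | Sign if the intervention works |
|---|---|---|
| Δ drug wasted | Item 1 | expected small, positive |
| Δ event costs | Item 2 (observed); item 3 (projected) | expected negative |
| Δ dispensing fees | Item 3 | expected negative |
| Δ drug used | not listed | positive |
| Delivery | not listed | zero or positive |

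**Step 3: direction.** Listed net cost − full net cost = −[Δ(drug used) + delivery]. If PDC rises, the first term in the bracket is positive, and the second cannot be negative. The listed net cost is then too low, whatever the prices.

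**Step 4: size in days of drug.** Extra covered days per class per patient over a full year = 365 × rise in mean PDC.

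- One-point rise: 365 × 0.01 = 3.65 days per class.
- The article gives no expected rise in mean PDC. The 10% in the Power Calculation section is a change in the share of patients reaching PDC ≥80%, which is a different quantity. Assume 2 to 10 points.
- The Secondary Outcomes section allows 1 to 4 classes per patient.
- Low end: 365 × 0.02 × 1 = 7.3 class-days per patient-year.
- High end: 365 × 0.10 × 4 = 146 class-days per patient-year.

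**Step 5: size in money.** This cannot be computed. The article gives no drug price, dispensing fee, event cost or delivery cost.

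**The case against.** The best defence is that the section states a hypothesis and a list of data to collect, not a costing model. It sets no perspective, neutrality margin or net-cost formula, and does not call the list exhaustive. A journal article may leave costing categories to a fuller plan, and the linked ODB data would permit total drug cost. This has force against any complaint of missing detail. It does not dispose of the point, because the article does enumerate the components, names wastage as the added drug cost, and argues in two places from surplus alone. For the hypothesis stated, that list is wrong and not merely short.

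On delivery, the defence is stronger. The stated economic objective concerns prolonged discharge prescriptions, only the hypothesis sentence refers to the package, and the ward visits are described as monitoring, so they may be study activity. A narrower perspective would be legitimate if the claim were narrowed to match.

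Several stronger readings are tempting but unsupported:

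- **Events are double counted.** Items 2 and 3 both concern events, but one is an observed difference and the other a projection. The article never says they will be added.
- **A formal cost-neutrality test is biased.** No such test is specified.
- **The conclusion would reverse.** Event and fee savings could still exceed the omitted costs.
- **The projection of over 30 events is wrong.** The gap from 29.5 is rounding.
- **The projection should shrink to the study cohort.** The 60 patients a month in the power calculation is per site and concerns patients aged 65 and older, whereas the projection covers all MIs in the region.
- **Extra drug-days can be divided by events avoided.** The projection assumes a 10% adherence gain, and the article does not link changes in mean PDC to events.

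**Conclusion.** The concern holds in a limited form. As listed, the evaluation omits the cost of additional drug dispensed and used through better adherence, and the cost of delivering the package. If adherence improves, both omissions push the apparent net cost toward the hypothesized result. The direction rests on two assumptions: that mean PDC rises, as the article expects, and that the listed items are what is costed.

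The drug omission is 3.65 days per class per patient-year for each one-point rise in mean PDC, or 7.3 to 146 class-days per patient-year under the assumed ranges. Its monetary size is unknown. The delivery omission matters only while the claim is made for the package as a whole. The point should be addressed because it affects a stated secondary objective; the primary adherence analysis is untouched.

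**What to change.** - **Drug cost.** Replace item 1 with the difference in total ODB drug cost per patient over 365 days, drug plus dispensing fees, with wastage as a sub-line. The fee reduction in item 3 then sits inside this total and should not be credited again.
- **Delivery.** Either add the delivery cost of each package, separately for intervention groups 1 and 2, or limit the cost-neutrality statement to prescription and event costs.
- **Events.** Report observed event costs (item 2) as the main result. Keep projected events (item 3) as a separate scenario that is not added to it.

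The cost is a change of wording and a little more analysis. According to the Data Sources section, ODB captures all dispensations for covered residents and is already to be linked. Delivery costs, if included, would have to come from the study team's own records. The downside is a possibly less favourable cost result.
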